## 6. Statistical plan

### 6.1. Sample size determination and power

Power and Sample size calculation are based on established formulae. Mean difference data (effect size) are based on studies in PD by Breen et al 2014, Dumpala et al 2019, Xu et al 2014, Videnovic et al 2017, Zulai et al 2019, Rehman et al 2019 and Paus & Schmitz-Hubsch 2007. A minimum sample size of 60 persons will be required to statistically detect a minimum meaningful difference as per outcome measures. This assumes a type I error of 5% (two tailed) and a type II error of 10% (90% power). We assume a response rate of 75% and allow 15% extra participants for multivariable statistical modelling to adjust for confounding factors (a 1.89x inflation).

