#### 4.3. Recruitment strategies, timeframe

We will allow an 18 months recruitment period. Recruitment strategies include approaching participants from the Movement Neuroscience group at QUT and our previous studies in PD if they have consented to be approached. It will further include approaching participants from Dance Parkinson's classes held at QUT (once a week), and media advertising (QUT media). One of the team members is a neurologist at the Mater hospital and he will provide information/flyers about the trial, however will not recruit or consent participants to avoid pressure and coercion. He will also contact patients from his clinical practise and obtain consent to pass their contact details to the QUT research team to discuss participation in the study. We anticipate to achieve the required number of participants (n = 60) through the above-mentioned avenues as previously shown in our studies. However, if required, will also expand our recruitment strategy through presentation of the clinical trial information by researchers, flyers provided to Parkinson's support groups, the Men's Shed community groups, and older people's community centres.

All resources are available at QUT and the team members have long-standing experience in all aspects of the protocols. We therefore do not foresee challenges in recruitment within this timeframe, however we can extend the timeline of recruitment if required. To retain participants throughout the study period (6 weeks) we will closely monitor engagement (4 home visits as well as 3 laboratory visits and frequent text message or calls during the intervention period). Our statistical methods also account for a 15 % drop out rate in case some of the participants cannot be retained.

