### 5.5. Data collection/gathering techniques:

1. Questionnaires for screening: Three validated questionnaires will be used to screen the PD participants stage of disease using the Movement Disorders Society Unified Parkinson's Disease Rating Scale (MDS-UPDRS), the Hoehn & Yahr scale to determine PD stage and severity and the Addenbrooke's Cognitive Examination (ACE) (score <82) for exclusion of dementia. We will also determine the participants chronotype using the Morningness Eveningness Questionnaire (MEQ), so the timing of the individual supplemental light intervention can be personalized (morning or evening light exposure).

Questionnaires at every lab visit: Participants will complete five additional validated questionnaires; the Pittsburgh Sleep quality index (PSQI), the Epworth Sleep Scale (EES), the Parkinson's Disease Sleep Scale (PDSS) to assess sleep behaviour, the Parkinson's Disease Questionnaire (PDQ-39) and the Beck's Depression Inventory-II to assess quality of life and mood, respectively. Participants will also complete a sleep diary to record sleep behaviour and subjectively determine sleep efficiency over 6 weeks. We have used this protocol including PSQI, ESS and sleep diary successfully in people with PD and in patients with diabetes.

2. As part of the screening, we will assess the health of the eye as per established ophthalmological examination (i.e. visual acuity, eye pressure, slit lamp, funduscopy, optical coherence tomography) performed in every clinic.
3. We will use pupillography, a device to measure the pupil diameter in response to a light stimulus to determine melanopsin cell function as per established standards and used in our laboratory in PD as well as diabetes and retinal/optic nerve diseases (i.e. current low risk QUT HREC approval no 1700000699). For measuring the pupil, the participant will place their head on a chin rest (similar to that used in an ophthalmic or optometric eye exam) and a short duration (1s) light stimulus will be directed towards the right eye whereas the other eye's pupil movements will be measured via an infrared camera and then analysed as per our established procedures in the laboratory.

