#### 5.6. **Impact of and response to missing data e.g. extrapolation; participant withdrawal**

Our statistical methods also allow for a 15 % drop out rate in case some of the participants cannot be retained. We can also extend our recruitment period to longer than 18 months and recruit more participants if required.

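### The 1.89x sample-size inflation in section 6.1 does not follow from its stated parts, so the 60-participant, 90% power statement cannot be reproduced

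*Combined protocol and SAP*

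**What the plan says.** Section 6.1 of the protocol (sample size and power) gives one number for the whole trial: "A minimum sample size of 60 persons will be required to statistically detect a minimum meaningful difference as per outcome measures". On error rates it says: "This assumes a type I error of 5% (two tailed) and a type II error of 10% (90% power". It then describes the inflation: "We assume a response rate of 75% and allow 15% extra participants for multivariable statistical modelling to adjust for confounding factors (a 1.89x inflation".

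Section 6.1 does not mention drop-out. Two other sections do. Section 4.3 (recruitment) says: "Our statistical methods also account for a 15 % drop out rate in case some of the participants cannot be retained". Section 5.6 (missing data) says: "Our statistical methods also allow for a 15 % drop out rate".

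For effect sizes, section 6.1 refers to published studies but prints no difference, no SD, no base number and no outcome that governs the calculation. It does not define the response rate. It does not say whether 60 is the number before or after inflation.

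**The concern.** The inflation sentence is the only step of the sample-size calculation that a reader can recompute, and its result does not match its inputs. In addition, section 6.1 assigns 15% to adjusted modelling, while sections 4.3 and 5.6 speak of 15% drop-out. It is unclear whether the plan contains one such allowance or two.

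At stake is how far the 90% power statement can be relied on when a null result is read. The number expected in the analysis, and so the difference the trial could detect, depends on which allowances were applied and on whether 60 already includes them. Nothing else in section 6.1 lets the reader settle this.

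**Working it through.** **Inputs.** From section 6.1: N = 60, two-sided 5% type I error, 90% power, 75% response rate, 15% extra for modelling, stated factor 1.89. From sections 4.3 and 5.6: 15% drop-out. The allocation ratio is not stated; 1:1 is assumed where it is needed.

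**Step 1. The plan's factor from its own two parts.**
- 15% added, 75% responding: 1.15/0.75 = 1.53.
- 15% applied as a loss: 1/(0.75 × 0.85) = 1.57.

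The printed 1.89 is not reproduced. Getting there from 1.53 takes a further factor of 1.89/1.533 = 1.23, too large for rounding.

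**Step 2. Drop-out as a second, separate 15%.**

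| Reading | Formula | Factor |
|---|---|---|
| Both added | 1.15²/0.75 | 1.76 |
| Modelling added, drop-out as loss | 1.15/(0.75 × 0.85) | 1.80 |
| Both as losses | 1/(0.75 × 0.85²) | 1.85 |
| Modelling added, losses summed | 1.15/(1 − 0.25 − 0.15) | 1.92 |

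These lie on both sides of 1.89, but none equals it.

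**Step 3. What the mismatch does to N.**
- If 60 is the inflated total, the base implied by 1.89 is 60/1.89 = 31.7, about 32. At 1.53x that base needs 32 × 1.533 = 49. The plan then has more participants than its stated parts require.
- If 60 is the uninflated number, the total would be 60 × 1.533 = 92, or 60 × 1.89 = 113.4, that is 114.

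**Step 4. What 60 randomised can detect.** The 90% power cannot be recomputed without a difference and an SD. The detectable standardised difference d can. For a two-sample t-test with n per arm, d solves P(T > t) = 0.90, where t is the 97.5% point of the t distribution on 2n − 2 degrees of freedom and T is noncentral t with noncentrality d√(n/2).
- All 60 analysed, n = 30 per arm: d = 0.85.
- 15% lost, 60 × 0.85 = 51 analysed, n = 25.5 per arm: d = 0.93.

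The normal approximation (1.960 + 1.282) × √(2/n) gives 0.84 and 0.91. All of these are before covariate adjustment.

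**The case against.** The strongest defence is that the plan may hold two different 15% allowances: one for modelling in section 6.1, and one for drop-out in sections 4.3 and 5.6. Those two sections refer to statistical methods, and section 6.2 says missing values are handled within the mixed model, so they need not describe an inflation of N at all. A reader might infer that a single 15% has been spent twice and that no drop-out allowance exists. The documents do not establish that.

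With two allowances, the result also comes close to the plan. Taking 32 and rounding up after each division gives 32/0.75 → 43, 43/0.85 → 51, 51/0.85 → 60. But 60/32 = 1.875, and this route needs a second 15% that section 6.1 does not list. One could also note that 1.15 × 1.15/0.70 = 1.889. That is conjecture: it replaces the stated 75% by 70%, so one printed figure would still be wrong.

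A reader might take the response rate to mean replies to invitations, which would not reduce the number analysed and should not inflate the number randomised. The term is undefined and could equally mean usable data, so the criticism holds only on the first meaning. For the same reason 1.53 is what the stated parts give, not a factor shown to be right.

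A reader might also infer lost power: a trial sized at 60 for 0.85 SD would have 85% power after 15% loss, and 73% after 25% and 15% losses combined. But 0.85 SD is solved back from N = 60; the plan does not state it as a target.

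What stands after all this is the mismatch itself and the missing inputs.

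**Conclusion.** The stated inflation does not follow from its stated parts: 1.53 to 1.57 against the printed 1.89. A separate 15% drop-out factor gives 1.76 to 1.92 over the variants tried, and none gives 1.89. As written, the 60-participant, 90% power statement is not reproducible, and the missing difference, SD, base number and governing outcome mean it cannot be checked by another route.

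A reader might go further and call the trial underpowered. The documents do not support that. If 60 is the inflated total, the discrepancy is on the conservative side (60 planned against about 49); only if 60 is the uninflated number does the plan fall short of its own allowances (92 to 114). The text does not say which applies. The N comparison uses no variance or allocation assumption; the detectable differences assume 1:1 allocation and an unadjusted two-sample t-test, whereas the planned analysis is an adjusted mixed model.

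**What to change.** In section 6.1:

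- Replace 1.89x with the factor that follows from the stated parts, and show the multiplication.
- Define the response rate, and keep it in the inflation only if it means loss of analysable data.
- List the modelling and drop-out allowances separately, and align sections 4.3 and 5.6 with them.
- Say whether 60 is before or after inflation.
- Name the primary outcome and time point that govern the calculation, with the difference, SD and base number. A choice is needed, because the primary endpoints cover several polysomnography measures and melatonin onset, at week 4 and week 6.

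If the original inputs cannot be recovered, replace the 90% power claim with the detectable difference for 60 randomised: 0.85 SD if all are analysed and 0.93 SD if 51 are analysed after 15% drop-out, with the assumptions given (two-sample t, 1:1, two-sided 5%, 90% power, no covariate adjustment). These figures say what N can detect, not what difference is worthwhile, and should be labelled so.

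The cost is rewording. The stated figure may look less favourable; no more participants are needed.

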### 6.2. Data analysis and statistical methods

Descriptive statistics will be calculated for demographic characteristics for the full study cohort and by light therapy study group. Categorical variables will be summarised as percentages and continuous variables will be summarised by medians, means with standard deviations. Participants will be analysed according to the light therapy group as randomised. Analysis will follow an intention to treat principle with missing values accounted for in the statistical model. Mixed models will be used to account for the longitudinal nature of the data, using intervention group, time point (baseline, week 4 and week 6) and interactions as explanatory variables to the primary, secondary and exploratory outcome measures in R applying packages. The fitted mixed models will be used in *post hoc* analyses with respect to group and time point to explore potential differences due to these two variables and their interaction. The mixed models will be adjusted for baseline characteristics including age, sex, Hoehn and Yahr disease stage, PD duration and levodopa equivalent daily dosage (LEDD).

## 7. Data management and record keeping

### 7.1. Confidentiality and privacy (including linkages)

The participants privacy and confidentiality will be respected throughout of this research. We will not use private information for any other purpose than for which it was provided for and reporting of data for will be un-identifiable so that they cannot be linked to a specific person. We will give participants due scope in the capacity to make their own decisions and empower and protect every participant where necessary.

### 7.2. Data security

Participant personal information (age, gender, date of birth) will be securely locked away in a drawer in the Medical Retina and the Movement Neuroscience laboratories with only the QUT research team having access (the key). Research data gained from participants for analysis will be coded and re-identifiable. Coded data

obtained from this study will be securely stored on the QUT research team's computers and archived in electronic format using the QUT Research Data Storage Service (RDSS) and the QUT U-drive in a special named folder, with access restricted (password) to the QUT Research team. The de-identified clinical data may be shared with The Michael J. Fox Foundation for Parkinson's Research (the study funder). The de-identified data will be kept on a central repository hosted by QUT and The Michael J. Fox Foundation, and will be kept indefinitely. Identifiable data will be retained for a period of 15 years, in accordance with the appropriate Retention Schedule. In order to advance scientific discoveries, de-identified data will be made publically available (with no personal identifying information) for the intended use of research in Parkinson's disease, as well as other biomedical research studies that may not be related to Parkinson's disease. Reporting of data (i.e. research publications, presentation at conferences) will be un-identifiable.

### 7.3. Record retention

Ophthalmic and PSG, motor function and questionnaire data will be archived on a computer (password coded) and/or locked away with only the research team members having access. Data will be destroyed as required after 15 years. Salivary samples will be disposed immediately after determination of Melatonin at the Adelaide Research Assay Facility.

### 7.4. Secondary use

N/A

## 8. Resources

- Resources necessary for the project to be conducted and makes it a feasible venture  
All resources are available within the research team and at their laboratories at QUT
- Funding/support, including any in-kind support, being sought or secured  
Funding has been awarded by the Michael J Fox Foundation and Shake It Up Australia Foundation therapeutic pipeline Program Clinical Stage Spring 2020 .

